## Abstract

**Background:**

The Screening Inventory of Psychosocial Problems (SIPP) is a short, validated self-reported questionnaire to identify psychosocial problems in Dutch cancer patients. The one-page 24-item questionnaire assesses physical complaints, psychological complaints and social and sexual problems. Very little is known about the effects of using the SIPP in consultation settings. Our study aims are to test the hypotheses that using the SIPP (a) may contribute to adequate referral to relevant psychosocial caregivers, (b) should facilitate communication between radiotherapists and cancer patients about psychosocial distress and (c) may prevent underdiagnosis of early symptoms reflecting psychosocial problems. This paper presents the design of a cluster randomised controlled trial (CRCT) evaluating the effectiveness of using the SIPP in cancer patients treated with radiotherapy.

**Methods/Design:**

A CRCT is developed using a Solomon four-group design (two intervention and two control groups) to evaluate the effects of using the SIPP. Radiotherapists, instead of cancer patients, are randomly allocated to the experimental or control groups. Within these groups, all included cancer patients are randomised into two subgroups: with and without pre-measurement. Self-reported assessments are conducted at four times: a pre-test at baseline before the first consultation and a post-test directly following the first consultation, and three and 12 months after baseline measurement. The primary outcome measures are the number and types of referrals of cancer patients with psychosocial problems to relevant (psychosocial) caregivers. The secondary outcome measures are patients' satisfaction with the radiotherapist-patient communication, psychosocial distress and quality of life. Furthermore, a process evaluation will be carried out. Data of the effect-evaluation will be analysed according to the intention-to-treat principle and data regarding the types of referrals to health care providers and patient satisfaction about the with radiotherapists will be analysed by means of descriptive techniques. The process evaluation data will also be analysed by means of descriptive techniques.

**Discussion:**

Using the SIPP may prevent underdiagnosis of early symptoms reflecting psychosocial problems, should facilitate communication between physicians and patients about psychosocial distress and may contribute to adequate referral to relevant (psychosocial) caregivers.

**Trial Registration:**

NCT00859768

## Background

Cancer is a leading cause of death worldwide, accountable for 7.9 million deaths (around 13% of all deaths) in 2007 [1]. Cancer and its treatment may lead to psychosocial distress involving symptoms of depression and anxiety, and turmoil in the lives of patients and their families [2,3]. Patients entering radiotherapy treatment (RT) suffer from specific distress such as fear of RT and its side effects [4]. The prevalence rates of psychosocial distress in cancer patients as reported in numerous studies vary from 5 to 53%, depending on the study population and the method of distress assessment [3,5-10].

Nevertheless, psychosocial distress in cancer patients is often underdiagnosed by medical staff in oncology settings [11,12]. Recognition and treatment of psychosocial distress in cancer patients is crucial [12,13]. Even when psychosocial distress is on a sub-clinical level, it should be managed to prevent further deterioration to psychiatric disorders like major depression or adjustment disorder [10]. Psychiatric disorders affect many oncology outcomes, such as compliance with therapy and quality of life [12]. Effective treatment of psychosocial distress may affect the course of the disease and improve patients' quality of life [13,14]. Therefore, it is important to identify and treat cancer patients with psychosocial distress at an early stage.

Validated screening instruments are useful tools to recognise psychosocial distress in cancer patients [2]. Besides recognition of psychosocial distress, self-reported questionnaires have proven to be good instruments to facilitate communication between patients and physicians with respect to psychosocial distress [12,15]. Although a number of well-validated screening instruments exist, including the Hospital Anxiety and Depression Scale [16], the Brief Symptom Inventory [5] and the General Health Questionnaire [17], these instruments require time and effort in administering and scoring, which may prevent their systematic use in clinical oncology settings [7,18,19]. Feasible screening instruments should meet the following criteria: be very brief, preferably fitting on one page[20]; be easy to complete (to avoid further distress by excessive questioning) [21]; be easy to score and interpret by medical staff [22]; and facilitate communication between physicians and patients about psychosocial distress [12,15]. The Screening Inventory Psychosocial Problems (SIPP) is a valid and reliable Dutch questionnaire (see methods section). The SIPP was specifically developed for use in Dutch cancer patients and for measuring a variety of distress symptoms [23].

Although the SIPP is being used in several hospitals and health care facilities in the Netherlands, there is still little known about the effects of using this questionnaire in consultation settings [23]. Therefore, we performed a study to assess the effectiveness of the SIPP in a clinical oncology setting. This paper presents the design of a cluster randomised controlled trial (CRCT) evaluating the effectiveness of using the SIPP in Dutch patients with the most common cancer types treated with radiotherapy.

### Aims

Primary aims are to study the effect of the SIPP on the number and types of referrals of cancer patients with psychosocial problems to psychosocial caregivers. Secondary aims are to study the effects of the SIPP on: 1) patients' satisfaction with the radiotherapist-patient communication during first consultation, 2) psychological distress in both the short- and long-term, and 3) quality of life in both the short- and long-term. Additionally, a process evaluation will be performed. The aim of the process evaluation is to gain insight into factors potentially influencing the effectiveness of the SIPP and factors facilitating future implementation of the SIPP in oncology care settings, if the SIPP proves to be effective.

## Methods/Design

### Study Design

The design of this study is a CRCT because it is less prone to contamination bias [24-26]. In addition, we used a Solomon four-group design. The Solomon four-group design is an experimental design with two experimental groups and two control groups (Figure 1). Pre-test measures are used for one experimental and one control group. Following exposure of both experimental groups to the intervention, post-test measures are assessed in all four groups.

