### Intervention

The SIPP is a short, valid and reliable 24-item self-reported questionnaire that systematically identifies psychosocial problems in Dutch cancer patients. The psychometric properties of the SIPP were studied in an as yet unpublished study (submitted, copy available upon request). This questionnaire was originally developed in the Netherlands by Pruyn and colleagues in 1997 (then named the Integral Checklist) [23], and was further adapted in several Dutch pilot studies [20,27]. The SIPP assesses:

• physical complaints (seven items, score range 0–14),

• psychological complaints (10 items, score range 0–20),

• social and financial problems (four items, score range 0–8), and

• sexual problems (three items, score range 0–6 with an additional option of "not applicable" (N/A)).

Items are rated on a three-point scale of 0 (no) to 2 (yes). Higher scores indicate poorer functioning.

Before the start of the study, the radiotherapists in the experimental condition are trained in using and interpreting the SIPP. According to the intervention procedure, the patient receives the SIPP at two different time points during their RT period: just before the first consultation with the radiotherapist (one to three weeks before starting RT) and before the last consultation with the radiotherapist at the end of the RT period (five to nine weeks after completing the first SIPP). At both times, the completed SIPP is handed to the radiotherapist at the start of the consultation. The radiotherapist checks the scores of the SIPP to get an overview of potential psychosocial problems and the patient's needs for psychosocial care. Psychosocial problems are discussed with the patient during the consultation. Referral to a psychosocial caregiver at the Institute Verbeeten in Tilburg occurs only with the permission of the patient.

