### Care as usual

Patients in the control group receive care as usual. No recent guidelines for the systematic assessment of psychosocial problems in cancer patients exist at the Institute Verbeeten. In the control group, radiotherapists may refer patients to psychosocial caregivers (social workers) at the Institute Verbeeten. However, this occurs according to the radiotherapist's judgment about the presence or absence of psychosocial problems in patients. Referrals to psychosocial caregivers at the Institute Verbeeten will be registered in both the patient's records and by the psychosocial caregivers.

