### Statistical analysis

Descriptive techniques will be used to describe patients' background characteristics. To detect potential differences between the experimental and control groups at the start of the study, the baseline levels of psychological distress and quality of life will be compared. Furthermore, to identify potential differences between the two experimental groups and the two control groups (both with and without pre-measurement) at T3 the extent of psychological distress and quality of life will be compared. If these latter differences emerge, the four groups need to be handled separately in the analyses, i.e. the experimental and control groups with pre-measurement and the experimental and control groups without pre-measurement will be compared separately. If not, the two experimental groups and the two control groups will be combined in one group.

Data of the effect evaluation will be analysed according to the intention-to-treat principle. Univariate, multivariate and descriptive techniques are applied to estimate the effect of the intervention by comparing the experimental with the control groups with regard to the primary and secondary outcomes at the follow-up measurements and by comparing the pre-test (T1) with post-tests (T3 and T4). Potential confounding factors and baseline differences will be checked and included in the model if necessary. Since dependency between outcome variables from the same cluster may exist, as well as between repeated measurements within patients, multilevel modelling will be carried out. Furthermore, multilevel modelling minimizes the loss of data through dropout by including all available data from participants in the analyses. Dropout will be described.

The process evaluation data (collected from radiotherapists and patients of the experimental groups) will be analysed by means of descriptive techniques.

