## Discussion

This study will provide insight into the actual systematic effects of using the SIPP in consultation settings. It is important to know the possible effects of using the SIPP on aspects such as communication between physicians and patients, early recognition and treatment of psychosocial problems, the extent and severity of experienced psychological problems among cancer patients and the quality of life of patients over a long period. Until now, there have been no RCTs on the effectiveness of the SIPP on aspects such as quality of life among cancer patients and the extent of psychological distress that cancer patients experience over a long period after the initial radiation or other treatment of the cancer. Until now, there have also been no reports on the differences in number of patients receiving psychosocial help because of using the SIPP.

The design of this study is a CRCT. Cluster randomisation is applied because randomisation at the patient level may jeopardise the validity of the study since patients of the experimental and control conditions may visit the same radiotherapist for consultation. Furthermore, radiotherapists may alter their communication style, attitude or may pay more attention to patients' psychosocial distress because of using the SIPP. The Solomon four-group design is chosen in order to check for potential pre-measurement effects on intervention outcomes [52,53].

In this study, we decided to include patients with the most common cancer types and with a reasonably good prognosis because patients were asked to complete questionnaires 12 months after baseline measurement.

One limitation of this study is that the results can not be generalised to all Dutch cancer patients since our study population consisted of cancer patients that received RT. Further studies outside the radiotherapy setting would be required to generalise the results.

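### The pooling rule relies on a pre-measurement check that is weak in the experimental arm and does not cover referral, so an effect of T1 on the primary outcome could go unseen and dilute the pooled SIPP estimate

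*Protocol article*

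**What the plan says.** Under Study Design, the article sets out two experimental and two control groups: "Pre-test measures are used for one experimental and one control group". It continues: "Following exposure of both experimental groups to the intervention, post-test measures are assessed in all four groups". The Discussion gives the reason: "The Solomon four-group design is chosen in order to check for potential pre-measurement effects on intervention outcomes".

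The Intervention section defines the treatment as a questionnaire: "The SIPP is a short, valid and reliable 24-item self-reported questionnaire that systematically identifies psychosocial problems in Dutch cancer patients". On timing it says "the patient receives the SIPP at two different time points during their RT period: just before the first consultation with the radiotherapist", and again before the last one. Training of the radiotherapist, hand-over of the form, review of the scores and discussion with the patient belong to the same procedure.

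Table 1 places the pre-test (T1) before the first consultation, in the pre-measured groups only. It consists of the HADS, the GHQ-12 and the EORTC QLQ-C30. Under Randomisation and stratification, odd-week patients get T1 and even-week patients do not. For the comparator: "Patients in the control group receive care as usual".

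Under Statistical analysis, the groups with and without pre-measurement are compared within each condition on distress and quality of life at T3. If differences emerge, experimental and control are compared separately by pre-measurement status. If not, "the two experimental groups and the two control groups will be combined in one group".

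**The concern.** A Solomon check asks whether being measured beforehand changes later outcomes. It shows this most clearly when measured patients are set against patients who filled in nothing. Here that contrast exists only in the control arm. Every experimental patient has already answered questions on physical, psychological, social and sexual complaints shortly before the consultation. If answering such questions prompts patients to raise problems, most of that prompting may already be present in both experimental groups, and T1 would add little. A null result in that arm is therefore weak evidence that T1 does nothing.

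The check also looks away from where a T1 effect would matter most. It names distress and quality of life at T3. It names neither referral, the primary outcome, nor the communication items at T2, which are collected directly after the consultation. A null result on the named outcomes leads to pooling, and the plan then provides for no separate even-week comparison. If T1 had raised referral among controls, the pooled contrast would understate SIPP versus care as usual, and nothing planned would show it.

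**Working it through.** **1. The plan's own figure.** Inputs from Sample size and power analysis: 2% versus 11%, one-sided 0.05, 80% power, design effect 1.13, 20% dropout.

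n = [1.645·√(2·0.065·0.935) + 0.842·√(0.02·0.98 + 0.11·0.89)]² / 0.09² = 91.7, so 92 per group. Then 4 × 92 = 368, and 368 × 1.13 / 0.80 = 520. The figure reproduces. Run backwards, 520 × 0.80 / 1.13 / 4 = 92 effective patients per cell. Each of the four groups is thus sized for a separate comparison.

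**2. Questionnaire items completed before the first consultation.** T1 = 14 + 12 + 30 = 56. SIPP = 7 + 10 + 4 + 3 = 24.

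| Group | T1 | SIPP | Total |
|---|---|---|---|
| Experimental, odd weeks | 56 | 24 | 80 |
| Experimental, even weeks | 0 | 24 | 24 |
| Control, odd weeks | 56 | 0 | 56 |
| Control, even weeks | 0 | 0 | 0 |

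With versus without pre-measurement is 80 against 24 in the experimental arm and 56 against 0 in the control arm. The even-week contrast is SIPP against no questionnaire. The odd-week contrast is SIPP plus T1 against T1.

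**3. What four cell means can identify.** With separate effects for T1, SIPP completion and SIPP use (hand-over and discussion), the four-column design matrix has rank 3. The completion and use columns are identical, so those two effects are aliased. They separate only if completing any symptom questionnaire is assumed to have one common effect.

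**4. Sensitivity of the planned check** (two-sided 0.05 assumed, 92 effective patients per cell). Power for a standardised difference d is Φ(d·√(92/2) − 1.96):
- d = 0.2: 27%
- d = 0.3: 53%
- 80% power requires d = (1.96 + 0.842)·√(2/92) = 0.41

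**5. Illustration on referral.** This is an assumption, since the documents give no figure. T1 alone raises odd-week control referral from 2% to c, the experimental rate stays at 11% in both weeks, and weeks are equally filled.

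| c | Even-week difference | Odd-week difference | Pooled difference | Power of pooled test (184 per arm, one-sided) |
|---|---|---|---|---|
| 2% | 9 points | 9 points | 9 points | 97% |
| 4% | 9 points | 7 points | 11 − (2 + 4)/2 = 8 points | 92% |
| 6% | 9 points | 5 points | 11 − (2 + 6)/2 = 7 points | 82% |

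The experimental with-versus-without contrast is zero in every row.

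**6. Precision of the proposed estimates** (95% half-widths, 92 per cell).
- Even-week contrast: 1.96·√[(0.11·0.89 + 0.02·0.98)/92] = 7.0 points. Pooled at the same rates, with 184 per arm: 5.0 points.
- Control-arm pre-measurement effect: 1.96·√[(0.02·0.98 + 0.04·0.96)/92] = 4.9 points for 2% versus 4%, and 5.6 points for 2% versus 6%. A two-sided test would have 12% and 28% power respectively.

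**The case against.** The strongest reply is that the design is described correctly. In Solomon terms the test is the outcome pre-test and the SIPP is the treatment. One experimental group does go without T1, as stated, and the control comparison with versus without T1 is already planned. All of this stands. What it leaves open is that the planned check names only T3 distress and quality of life, while the Discussion presents the design as a check on intervention outcomes generally.

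Three stronger readings are tempting, and the documents do not support them.

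- A reader might infer that the trial fails because it cannot separate completing the SIPP from discussing it. The aims concern the SIPP as a package, and completion is part of that package. Comparing even-week experimental with odd-week control patients would not isolate discussion either. Completion and use are aliased, and that contrast also mixes instruments, weeks, and trained with untrained radiotherapists.
- A reader might infer that half the controls are not in care as usual. They receive usual clinical care with research questionnaires added, and nowhere is T1 said to be shown to the radiotherapist.
- A reader might infer that T1 and the SIPP are filled in at the same moment. T1 is placed only before the first consultation, and the interval is not given.

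Two further points are fair: the size of any T1 effect is unknown, and the dilution illustrated here would work against the SIPP, not for it.

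**Conclusion.** The point holds as a limit on the pooling rule and on how its check may be read. The experimental with-versus-without contrast is a weak test for a pre-measurement effect, the control arm carries most of the information, and the outcome that matters most is not among those checked.

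Under the assumed control rates of 4–6%, the pooled difference falls 1–2 points short of the 9-point even-week difference. This rests on a T1 effect that the documents neither state nor exclude, on T1 adding nothing to referral in the SIPP arm, and on an even split of weeks. Without a T1 effect on referral the shortfall is zero. In this range the pooled test keeps at least the planned 80% power, so what is at risk is mainly the estimate and its interpretation. The package effect and the sample size are not called into question.

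**What to change.** Two additions to Statistical analysis:

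1. Estimate the pre-measurement effect on referral and on the T2 communication items as well as on T3 distress and quality of life. Read it mainly from the control arm and report it as an estimate with an interval. A non-significant test at about 92 per cell should not be taken as showing no effect.
2. Whatever the T3 check shows, report the even-week experimental versus control contrast on referral beside the pooled result, labelled as the estimate of SIPP versus care as usual.

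Neither contrast should be presented as isolating hand-over or discussion of the SIPP.

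The cost is analysis and wording only, with no new data or patients. The even-week estimate uses half the patients, so its interval is about ±7 points against about ±5 pooled. The control-arm estimate will be imprecise, at about ±5 to 6 points in the range illustrated.

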**Figure 1 F1:**
[figure not shown]
**General description of the Solomon four-group design **[53]. O: Observation. X: Intervention.

### Intervention

The SIPP is a short, valid and reliable 24-item self-reported questionnaire that systematically identifies psychosocial problems in Dutch cancer patients. The psychometric properties of the SIPP were studied in an as yet unpublished study (submitted, copy available upon request). This questionnaire was originally developed in the Netherlands by Pruyn and colleagues in 1997 (then named the Integral Checklist) [23], and was further adapted in several Dutch pilot studies [20,27]. The SIPP assesses:

• physical complaints (seven items, score range 0–14),

• psychological complaints (10 items, score range 0–20),

• social and financial problems (four items, score range 0–8), and

• sexual problems (three items, score range 0–6 with an additional option of "not applicable" (N/A)).

Items are rated on a three-point scale of 0 (no) to 2 (yes). Higher scores indicate poorer functioning.

Before the start of the study, the radiotherapists in the experimental condition are trained in using and interpreting the SIPP. According to the intervention procedure, the patient receives the SIPP at two different time points during their RT period: just before the first consultation with the radiotherapist (one to three weeks before starting RT) and before the last consultation with the radiotherapist at the end of the RT period (five to nine weeks after completing the first SIPP). At both times, the completed SIPP is handed to the radiotherapist at the start of the consultation. The radiotherapist checks the scores of the SIPP to get an overview of potential psychosocial problems and the patient's needs for psychosocial care. Psychosocial problems are discussed with the patient during the consultation. Referral to a psychosocial caregiver at the Institute Verbeeten in Tilburg occurs only with the permission of the patient.

